### Intervention description {11a}

#### Randomization and intervention

Upon providing written informed consent, participants will be randomly allocated in a 1:1 ratio to either the experimental or control group. The experimental group will receive active treatment with liraglutide injections, whereas the control group will receive matching placebo injections. Treatment protocols will be determined by two endocrinologists and a psychiatrist involved in screening. Both groups will receive identical standard care, including diabetes-specific dietary plans and exercise guidance throughout the 12-week study period. Outcomes will be assessed at four time points: baseline and weeks 4, 8, and 12 (dual assessment at week 12 for the interim and final evaluations).

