### Relevant concomitant care permitted or prohibited during the trial {11d}

Throughout the study, foundational treatment will be emphasized for patients with diabetes. Participants are permitted to continue their pre-existing, stable (≥4 weeks of use prior to enrollment) conventional glucose-lowering medications—including metformin, sulfonylureas, sodium-glucose cotransporter-2 inhibitors, insulin and its analogues—in addition to the investigational product (liraglutide or placebo), in order to comply with ethical standards and maintain glycemic stability, while the initiation or switch to dipeptidyl peptidase-4 inhibitors, other GLP-1 receptor agonists, and related preparations is strictly prohibited. To ensure comparability of background therapy between groups, we will implement stratified randomization based on baseline insulin use and will meticulously record and compare all baseline glucose-lowering medications across groups prior to analysis to confirm randomization balance.

For the basic treatment protocol, the study will adhere to the recommendations outlined in the Chinese Diabetes Prevention and Treatment Guidelines (2020 edition).

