### Participant timeline {13}

Outcome assessments will be performed at baseline, followed by three subsequent visits. At baseline assessment, we will gather data on patient demographics, including age, gender, educational level, employment status, marital status, and comorbidities. Additionally, we will document the date of initial diagnosis, symptom duration, and details of prior medications and treatment regimens. The participants are required to revisit the hospital at 4, 8, and 12 weeks after medication initiation for a series of evaluations. These include height and weight measurements, completion of pertinent laboratory tests, and the administration of depression and cognitive function scales. These assessments aim to provide a comprehensive evaluation of treatment efficacy. The detailed enrollment process and comprehensive schedule of the evaluation results are presented in **Table 3**.

**Table 3 T3:** Schedule of outcome measures and trial-related activities.

Items	Enrollment day	4 weeks	8weeks	12 weeks
Inclusion screening				
Sign informed consent	*√*			
Record general information	*√*			
Gender	*√*			
Age	*√*			
Body weight	*√*	*√*	*√*	*√*
height	*√*	*√*	*√*	*√*
Waist circumference	*√*	*√*	*√*	*√*
Hip circumference	*√*	*√*	*√*	*√*
Medical history and treatment history	*√*			
Combined disease and medication records	*√*			
life history	*√*			
Safety				
blood routine examination	*√*			*√*
routine urine test	*√*			*√*
stool routine examination	*√*			*√*
liver function	*√*			*√*
renal function	*√*			*√*
Electrocardiograph	*√*			*√*
Adverse events and complications		*√*	*√*	*√*
Efficacy index				
Hamilton Depression Scale 24 scores	*√*			*√*
Blood glucose (fasting and 2 hours after meals)	*√*			*√*
glycosylated hemoglobin	*√*			*√*
blood lipids	*√*			*√*
tumor necrosis factor-α, Interleukin-6	*√*			*√*
super Oxide Dismutase,malondialdehyde	*√*			*√*
HOMA Insulin resistance Index	*√*			*√*
Insulin sensitivity Index	*√*			*√*
HOMA Islet beta Cell Function Index	*√*			*√*
resting-state functional magnetic resonance imaging	*√*			*√*

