### Statistical methods

#### Statistical methods for primary and secondary outcomes {20a}

The aim of this study is to compare the effectiveness of the two treatment regimens by assessing participants twice, once at baseline and again at the 3-month follow-up. To control for potential confounding variables, we will statistically adjust for participants’ age, gender, body mass index, and Hamilton Depression Rating Scale scores in accordance with the STRIVE criteria. Numbers and percentages will be used to express categorical variables and median and interquartile range will be used for continuous variables. Primary outcome measures (e.g., HAMD score, HbA1c, body weight) will be analyzed using Linear Mixed-Effects Models. The models will include treatment group, time, and the group-by-time interaction as fixed effects to test for between-group differences in treatment effect and its change over time. Subject-specific intercepts will be included as random effects. Analyses will be adjusted for pre-specified confounding variables, including age, sex, baseline BMI, and baseline HAMD score, which will be entered into the models as fixed-effect covariates. For missing data due to dropout, Multiple Imputation will be employed. Secondary outcomes and baseline characteristics will be described and compared as originally planned. All analyses will be performed using SPSS v.22.0 (SPSS Inc., Chicago, IL, USA) and the lme4 package in R. A p-value < 0.05 will be considered statistically significant, whereas a p-value <0.01 will be regarded as indicating a high degree of statistical significance.

The DPABI v6.0 toolkit will be used to perform two-sample t-tests on the whole-brain ALFF, ReHo, and VMHC maps of the two groups of participants. To correct for multiple comparisons across voxels, the statistical significance of the resulting maps will be assessed using Gaussian Random Field (GRF) theory, a method for family-wise error (FWE) rate correction. The threshold was set at a voxel-level significance of P < 0.001 and a cluster-level significance of P < 0.05.

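### In the planned mixed model baseline HAMD is both response and covariate: the listed adjustment cannot move the treatment effect, and the HAMD standard error is too small

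*Protocol article*

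**What the plan says.** All references are to the protocol article.

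- **Model, section {20a}.** "Primary outcome measures (e.g., HAMD score, HbA1c, body weight) will be analyzed using Linear Mixed-Effects Models". The fixed part of that model is then set out: "The models will include treatment group, time, and the group-by-time interaction as fixed effects". On the random part, the section adds: "Subject-specific intercepts will be included as random effects". The confounders are listed as "including age, sex, baseline BMI, and baseline HAMD score, which will be entered into the models as fixed-effect covariates".
- **Assessments in the analysis, section {20a}.** The comparison is made by "assessing participants twice, once at baseline and again at the 3-month follow-up".
- **Schedule, Table 3 in section {13}.** The row "Hamilton Depression Scale 24 scores" is ticked at enrollment and week 12 only, as are HbA1c, glucose and lipids. Weight and height are ticked at all four visits.
- **Conflicting schedule.** The subsection on randomization and intervention in {11a} states "Outcomes will be assessed at four time points: baseline and weeks 4, 8, and 12". The prose of section {13} also has depression scales administered at weeks 4, 8 and 12.
- **Randomization, section {11d}.** "we will implement stratified randomization based on baseline insulin use". Insulin use is not among the covariates in {20a}.

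**The concern.** With one post-baseline assessment, time and group-by-time can be estimated only if the baseline value is itself a row of the response. The article does not say this in words, but its two-assessment analysis leaves no other way to fit the model. Baseline HAMD is then a response and a predictor of itself.

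Two things follow. First, a covariate that is constant over time shifts both rows of a participant equally and drops out of the within-person change. The effect reported as adjusted would be the unadjusted difference in change. Second, in the HAMD model the baseline covariate absorbs so much between-person variation that the random-intercept variance is driven to zero, and the residual variance is understated. The HAMD p-value and confidence interval are then too optimistic for the outcome on which the trial focuses.

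The other outcomes have different and separate weaknesses: no own-baseline adjustment for HbA1c, glucose and lipids, and a restrictive correlation assumption for weight and BMI.

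**Working it through.** **Inputs.** From the article: 30 per arm, threshold p < 0.05 (taken as two-sided), and the model and schedule above. The planned size reproduces: 25/(1 − 0.15) = 29.4, so 30 per arm and 60 in total. The article gives no SDs, correlations or standard errors for this model. The baseline-to-week-12 correlation ρ and the ratio r = week-12 SD / baseline SD are therefore assumptions, with baseline SD set to 1.

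**Step 1: the estimate does not move.** Mixed models were fitted by REML to one simulated two-visit data set (ρ = 0.5, baseline imbalance between arms built in):

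| Model | Effect | SE | Random-intercept variance |
|---|---|---|---|
| Planned model, no covariates | −4.4037 | 1.286 | 15.29 |
| + age, sex, BMI, baseline HAMD | −4.4037 | 1.207 | 0 |
| + insulin use | −4.4037 | 1.207 | 0 |
| Raw difference in mean change | −4.4037 | | |
| Week-12 ANCOVA, same four covariates | −3.07 | 1.251 | |
| Week-12 ANCOVA + insulin use | −3.12 | 1.249 | |

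The covariates leave the interaction untouched and only shrink its standard error.

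**Step 2: why the HAMD standard error is too small.** Within persons, σe² is estimated by Var(change)/2 = (1 + r² − 2ρr)/2. Between persons, after regression on baseline, σe² + 2σu² is estimated by r²(1 − ρ²)/2. Subtracting gives σu² = −(1 − ρr)²/4, which is never positive, so the fit sits at zero. REML then pools the two strata (nearly equal degrees of freedom):

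model variance / true variance = 1/2 + r²(1 − ρ²) / [2(1 + r² − 2ρr)], which is (3 + ρ)/4 at r = 1.

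At r = 1 and ρ = 0.3 this is 0.825. Its root is 0.908, the critical value is effectively 1.96 × 0.908 = 1.78, and the type I error is 7.5%.

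Type I error for HAMD by this formula:

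| r | ρ = 0.3 | ρ = 0.5 | ρ = 0.7 |
|---|---|---|---|
| 0.8 | 8.9% | 8.2% | 7.7% |
| 1.0 | 7.5% | 6.7% | 5.9% |
| 1.2 | 6.6% | 5.8% | 5.2% |
| 1.5 | 5.8% | 5.2% | 5.0% |

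Separate simulations at r = 1 gave 7.6–7.9%, 6.6–7.0% and 5.9–6.1%. The variance was at zero in about 95–100% of trials, and the model SE was 0.91, 0.94 and 0.97 of the true SD. With 12.5% random dropout and no imputation (2,000 trials per setting), type I error was 8–9%. Week-12 ANCOVA held 4.7–5.2%.

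**Step 3: HbA1c, glucose, lipids.** Their own baseline is not a covariate, so the collapse does not occur. The HbA1c simulation gave an SE ratio of 0.99 and type I error of 5.1%; glucose and lipids share that structure. The loss is precision. The large-sample variance of ANCOVA relative to change is (1 + ρ)/2, a saving of 35%, 25% and 15% at ρ = 0.3, 0.5 and 0.7. With all four covariates fitted at 30 per arm, the simulated saving is smaller, about 29%, 20% and 8%.

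**Step 4: weight and BMI, four visits.** With equal correlation, the between-person component after baseline adjustment is (1 − ρ)(3 + 9ρ)/4. This exceeds the within-person (1 − ρ) whenever ρ > 1/9, so the variance does not collapse (zero in at most about 0.2% of simulated trials) and type I error is about 5%. Under serial correlation, the model takes the variance of the week-12 change as 2(1 − mean pairwise correlation), while the true value is 2(1 − ρ³), ρ now being the adjacent-visit correlation. At ρ = 0.7 the mean is (3×0.7 + 2×0.49 + 0.343)/6 = 0.5705, so 0.859 against 1.314, a ratio of 0.654 and type I error of 11.3%. At 0.6 and 0.8 the formula gives 10.2% and 12.4%. Simulation over 0.6 to 0.8 gave roughly 10–13%.

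**The case against.** **The HAMD schedule is unsettled.** Section {11a} and the prose of {13} point to HAMD at weeks 4, 8 and 12. On that reading, a model of the three post-baseline visits with baseline HAMD as covariate would be standard. This stands as a condition: the schedule must be reconciled first. It does not rescue {20a}, which describes its own analysis as two assessments and agrees with Table 3.

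**The sizes rest on assumed figures.** This stands. Entry requires HAMD of 8 to 35, which may narrow the baseline SD and push r above 1, where the inflation fades. With r below 1 it grows.

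**This is a pilot sized for precision, not testing.** This tempers the weight of a 6–8% error rate. But {20a} sets a significance threshold, and an understated standard error also makes the confidence interval too narrow, which defeats a precision aim directly.

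**Change scores are valid, and covariance details can wait for an analysis plan.** The first part is right for HbA1c, glucose and lipids: only precision is lost, and little at high correlation. On the second, the article does fix a random intercept as its only stated correlation structure.

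**Stronger readings that the article does not support.** A reader might infer that every standard error is too small; in two-visit data this is material only for HAMD. A reader might infer that BMI suffers the same collapse because its baseline is also a covariate; Table 3 gives weight and height at four visits, and there it does not. A reader might infer that adding insulin use to the stated model repairs it; as a main effect it leaves the interaction unchanged too.

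**Conclusion.** The point holds, mainly for HAMD and on the two-assessment analysis that {20a} describes.

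- **Adjustment.** In complete data, the listed covariates do nothing to the group-by-time estimate for any two-visit outcome. This is exact and needs no assumption about ρ or r. With missing week-12 values it is only approximate, and {20a} and {20c} disagree on whether these are imputed.
- **HAMD.** Type I error is about 8%, 7% and 6% at assumed correlations of 0.3, 0.5 and 0.7 with equal SDs. It falls to about 5–7% if the week-12 SD is 1.2 to 1.5 times baseline and rises to about 8–9% if it is 0.8 times baseline.
- **HbA1c, glucose, lipids.** Inference is valid, with avoidable loss of precision at low to moderate correlation.
- **Weight and BMI.** About 5% under equal correlation between visits, and roughly 10–13% under assumed serial correlation of 0.6 to 0.8.
- **Insulin stratum.** It is used in randomization and absent from the listed covariates, but it matters for the effect estimate only once baseline leaves the response.

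**What to change.** 1. Reconcile the HAMD schedule: {11a} and the prose of {13} against Table 3 and {20a}.
2. Model post-baseline values only. Use week 12 alone where that is the single follow-up, or weeks 4, 8 and 12 as categorical time with an unstructured covariance where the outcome is measured at each. Do not keep baseline as both response and covariate.
3. Adjust for the outcome's own baseline, age, sex and the insulin-use randomization stratum.
4. Report the adjusted week-12 difference between groups with its 95% confidence interval.

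The cost is a few lines of analysis wording and no new data. SPSS, already named in {20a}, can fit these models, although the article names no specific procedure. The downside is small: when the baseline-to-week-12 correlation is high there is little precision to gain.

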### Efficacy indicators

#### Primary outcome measures

1) Efficacy indicators include fasting plasma glucose, 2-hour postprandial glucose, body mass index (BMI), glycated hemoglobin (HbA1c), and lipid profiles (total cholesterol, triglycerides, low-density lipoprotein cholesterol, and high-density lipoprotein cholesterol).2) Depression scale scores, derived from the Hamilton Depression Scale (HAMD), will be used to assess the severity of depressive symptoms. This validated clinical tool provides quantifiable measurements of both condition severity and treatment response in depression management (27).3) Resting-state functional magnetic resonance imaging parameters comprise three key metrics: the amplitude of low-frequency fluctuations (ALFF), regional homogeneity (ReHo), and functional connectivity (FC). These biomarkers quantitatively reflect spontaneous neural activity patterns and dynamic connectivity alterations across brain networks. They are widely employed in neuropsychiatric research, particularly in depression studies (28).

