### Preprocessing and index calculation of rs-fMRI data

All preprocessing will be performed using the DPABI v6.0 toolbox in MATLAB software (29). To achieve data balance, the first 10 time points of each participant’s data will be excluded. Subsequently, the following preprocessing steps will be implemented: (1) temporal layer correction; (2) head motion correction, with exclusion of data if the participant’s head translation exceeds 2 mm or rotation exceeds 2°; (3) covariate regression (including Friston 24 head motion parameters, global brain signal, white matter signal, and cerebrospinal fluid signal); (4) spatial normalization (resampling voxel size to 3 mm × 3 mm × 3 mm); (5) spatial smoothing (Gaussian kernel full width at half maximum of 6 mm); (6) removal of linear drift; and (7) band-pass filtering (bandwidth of 0.01–0.10 Hz).

Resting-state brain functional indices will be derived using DPABI v6.0. The amplitude of low-frequency fluctuations will be computed after the aforementioned preprocessing stages, focusing on ALFF values within the frequency range of 0.01–0.08 Hz. The regional homogeneity values reflect Kendall’s coefficient of concordance, encompassing a voxel and its 26 neighboring voxels. Spatial smoothing will not be applied during preprocessing; however, Gaussian smoothing will be conducted after computation using a smoothing kernel diameter of 6 mm.

Given the asymmetry of the human brain, a symmetric template in the standard space will be constructed from the T1-weighted structural images of all participants. This template will subsequently be utilized to re-standardize the functional images. Following spatial smoothing, removal of linear drift, and filtering, the Pearson correlation coefficient between symmetric voxels across both cerebral hemispheres will be calculated as the mean volume homogeneity correlation value. These indices will undergo Fisher-z transformation to generate z-values, which will then be used for further statistical analysis.

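### The fMRI connectivity outcome that is declared primary (FC) is not the one derived and tested (VMHC), and the fMRI t-test does not fix which maps are compared or name a baseline adjustment

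*Protocol article*

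**What the plan says.** All references are to the protocol article.

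- **Primary outcome measures** lists "three key metrics: the amplitude of low-frequency fluctuations (ALFF), regional homogeneity (ReHo), and functional connectivity (FC"), and says that these metrics reflect "spontaneous neural activity patterns and dynamic connectivity alterations across brain networks".
- **Preprocessing and index calculation of rs-fMRI data** derives ALFF, ReHo and one further index: "the Pearson correlation coefficient between symmetric voxels across both cerebral hemispheres will be calculated as the mean volume homogeneity correlation value". It describes no seed-based, region-based or network-based connectivity measure.
- **Statistical methods {20a}** opens by describing the comparison as "assessing participants twice, once at baseline and again at the 3-month follow-up". It gives primary outcomes (its examples are HAMD, HbA1c and body weight) a linear mixed model with group, time and group-by-time, adjusted for age, sex, baseline BMI and baseline HAMD. For imaging it then plans to "perform two-sample t-tests on the whole-brain ALFF, ReHo, and VMHC maps of the two groups of participants", with Gaussian random field correction at voxel P < 0.001 and cluster P < 0.05.
- **Table 3** schedules "resting-state functional magnetic resonance imaging" at enrollment and at week 12.
- **Section {20b}** plans no analysis beyond those in {20a}.

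**The concern.** There are two problems, both in a declared primary outcome.

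**Outcome mismatch.** The declared set and the tested set differ in one member. FC is promised but has no derivation and no test. VMHC is tested but is not declared. If this stays, either a declared primary outcome has no result, or FC is defined after the data are in, with seeds, networks and thresholds still to choose.

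**Unfixed contrast.** Each participant has two scans, but the imaging sentence names no visit, no change map and no baseline map. It also departs, without explanation, from the group-by-time model given for primary outcomes in the same section. The analyst could compare week-12 maps or change maps, and these can give different answers from the same data. Neither choice uses the baseline scan as efficiently as direct adjustment for it.

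**Working it through.** **1. The sections side by side**

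| Section | Metric 1 | Metric 2 | Metric 3 |
|---|---|---|---|
| Primary outcome measures | ALFF | ReHo | FC |
| Preprocessing | ALFF | ReHo | mirror-voxel correlation |
| Statistical methods {20a} | ALFF | ReHo | VMHC |

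The second and third rows agree in substance, because "the Pearson correlation coefficient between symmetric voxels across both cerebral hemispheres will be calculated" is what a VMHC map contains. The abbreviation itself appears only in {20a} and is not spelled out. The first row differs. A mirror-voxel index covers one pair per location, whereas the outcome text speaks of connectivity across networks. No section equates the two, and {20b} rules out a further analysis elsewhere in this document.

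**2. The plan's own figures**

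The article gives no power or effect size for imaging. Its sample size section starts from 25 per group and a dropout of 10% to 15%. At 15%, 25 / 0.85 = 29.4, so 30 per group and 60 in total, which reproduces the stated 60. I use 25 completers per arm below.

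**3. What baseline adjustment is worth**

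Let ρ be the correlation between a participant's baseline and week-12 values at a voxel. The documents do not give it; I assume 0.3, 0.5 and 0.7. With equal variance at both visits, the variance of the between-group contrast relative to a week-12-only t-test is:

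- week 12 only: 1
- change maps (week 12 minus baseline): 2(1 − ρ)
- week 12 adjusted for the baseline map (ANCOVA): 1 − ρ²

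The ratio of ANCOVA to change maps is (1 − ρ²) / [2(1 − ρ)] = (1 + ρ)/2.

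| ρ (assumed) | Change v week 12 only | ANCOVA v week 12 only | ANCOVA v change |
|---|---|---|---|
| 0.3 | 1.40 | 0.91 | 0.65 |
| 0.5 | 1.00 | 0.75 | 0.75 |
| 0.7 | 0.60 | 0.51 | 0.85 |

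ANCOVA is the most precise of the three at every value shown. Change maps are worse than ignoring the baseline scan at ρ = 0.3 and no better at ρ = 0.5.

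**4. In terms of detectable difference**

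For a single measure with 25 per arm, two-sided 0.05 and 80% power (normal approximation), the detectable standardized difference is (1.960 + 0.842) × √(2/25) = 0.79 for week 12 only. Multiplying by √(1 − ρ²) gives 0.76, 0.69 and 0.57. These values illustrate scale only; they are not the power of a whole-brain, cluster-corrected test.

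**The case against.** **VMHC may be what was meant by FC.** As derived, it is a correlation between the signals of paired voxels, followed by a Fisher-z transformation, so it is a connectivity measure. Three metrics are declared, three derived and three tested, and VMHC sits in the third place. A reader might infer that a primary outcome was dropped and an unrelated one substituted; the documents do not support that. A general label made specific later is at least as likely. It still stands that no section says so and that the declared description is broader.

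**The baseline scan may be used.** A reader might infer that it is ignored. The text does not say this: a two-sample t-test on week-12-minus-baseline maps fits the sentence. What stands is that the maps are not named and no baseline adjustment is given.

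**A week-12-only test is valid.** A reader might infer bias from chance baseline differences. Under randomization the comparison is unbiased, and its standard error already allows for those differences. The loss is precision.

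**Multiplicity across maps.** Three map types at 0.05 each would give 1 − 0.95³ = 14.3% if independent, which may suggest splitting alpha. The documents give weak grounds for that. All three indices come from the same time series, the within-map correction is already specified, and the pilot is said to be sized for precision rather than hypothesis testing. Many other primary measures are also unadjusted, so a split for imaging alone would be a matter of preference.

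**Conclusion.** The mismatch between declared FC and tested VMHC is a contradiction within the document and must be reconciled, because it concerns a primary outcome. It rests on the text alone.

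The imaging contrast is also badly fixed: the test is stated, but the maps it applies to are not, and no baseline map enters. Adjusting week-12 maps for the baseline map would cut variance by 9%, 25% or 49% relative to a week-12-only test, or by 35%, 25% or 15% relative to change maps, at ρ of 0.3, 0.5 and 0.7. These figures depend on the assumed ρ, which will vary across the brain, and on similar variance at the two visits. They measure lost efficiency and leave the validity of the planned test untouched.

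**What to change.** 1. Make Primary outcome measures, the preprocessing section and {20a} agree before unblinding. Either name VMHC as the declared connectivity metric, spell it out and use one name throughout, or define FC (seeds, regions or networks, and the summary used) and add its test.
2. Replace the two-sample t-test by a voxelwise comparison of week-12 maps between groups, adjusted for the participant's own baseline map, and keep the stated random field thresholds. Do not offer change maps as an equivalent alternative, since they lose precision when ρ is below 0.5.
3. No division of alpha across map types is asked for.

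The cost is wording and a somewhat more elaborate voxelwise model; both scans are already scheduled. The team should confirm that its software accepts a voxelwise covariate. It should also state how a participant with only one usable scan is handled, because the head-motion exclusion can remove either scan.

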### MRI acquisition protocol

Neuroimaging data will be acquired using a Siemens 3T Trio MRI system (Erlangen, Germany) equipped with an 8-channel phased-array head coil. Prior to scanning, the participants will receive standardized instructions to maintain their eyes closed, relax without focused thinking, and minimize head motion during acquisition. For obtaining sagittal T1-weighted imaging structural images, a three-dimensional magnetization-prepared rapid gradient echo sequence will be employed, with the following specific parameters: TR 1900 ms, TE 2.52 ms, TI 900 ms, a flip angle of 9°, 160 slices, a voxel size of 1 mm × 1 mm × 1 mm, a field of view of 250 mm × 250 mm, and a matrix resolution of 256 × 256. Resting-state brain functional images will be acquired using a planar gradient echo sequence with the following specific parameters: TR 2000 ms, echo time 30 ms, flip angle 90°, 33 slices, slice thickness 4 mm. field of view 240 mm × 240 mm, matrix 64 × 64, and total acquisition 200 time points. Furthermore, conventional T2-weighted imaging and fluid-attenuated inversion recovery sequences will be used to exclude potential white matter degeneration or lacunar infarct foci.

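### Head motion is handled only within each scan; the group imaging test has no motion term, so residual motion that differs between arms could pass undetected as an imaging effect of liraglutide.

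*Protocol article*

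**What the plan says.** The protocol's Outcomes section lists resting-state fMRI metrics, among them ALFF and ReHo, as primary outcome measures. Section 20a gives their group-level test as "two-sample t-tests on the whole-brain ALFF, ReHo, and VMHC maps", with Gaussian Random Field correction at voxel P < 0.001 and cluster P < 0.05. It names no covariate in that sentence and does not say which scan is compared.

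Elsewhere, section 20a opens with a general statement, "we will statistically adjust for participants’ age, gender, body mass index, and Hamilton Depression Rating Scale scores". Later, directly after describing the mixed models, it says "Analyses will be adjusted for pre-specified confounding variables, including age, sex, baseline BMI, and baseline HAMD score". Neither list contains head motion.

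Motion is addressed earlier in the pipeline. Under MRI acquisition protocol, participants are instructed to "minimize head motion during acquisition". Under Preprocessing and index calculation of rs-fMRI data, the plan includes "head motion correction, with exclusion of data if the participant’s head translation exceeds 2 mm or rotation exceeds 2" degrees. It then regresses the Friston 24 motion parameters and the global, white-matter and cerebrospinal-fluid signals from each participant's data. Section 20b plans no analyses beyond those in 20a.

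**The concern.** Every motion step in the plan works on one scan at a time. Regressing motion parameters out of a participant's time series removes what those regressors fit linearly in that series. It does not guarantee that the resulting ALFF, ReHo or VMHC value is uncorrelated, across participants, with how much each person moved. Scans below the exclusion limits are kept, and no group-level term picks up what is left.

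Randomisation balances motion in expectation at baseline, but not necessarily on treatment. Table 3 schedules imaging only at enrolment and week 12, so an on-treatment comparison must use the week-12 scan, directly or as a change from baseline. By then the arms may differ in body weight, which the drug is expected to change, and in tolerance of treatment, for which the protocol plans dose reduction and removal. Whether either affects head motion is conjecture as far as the documents go, but the plan would not reveal it if it did. Motion exclusions also fall after randomisation, and no count by arm is stated.

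At stake is the interpretation of a primary outcome. The cluster correction controls chance clusters and does not remove a systematic shift between arms.

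**Working it through.** **The plan's own figure.** The documents give no motion, ALFF or ReHo figure to reproduce. The only usable input is the number of participants. The Sample size section takes 25 per group as the minimum and assumes 10% to 15% dropout: 25 / (1 − 0.15) = 29.4, rounded up to 30 per arm, or 60 in total. This matches the stated 60. I therefore use 25 scans per arm; exclusions for motion could reduce it further.

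**How far the retained motion can go.** The translation ceiling is 2 mm. Against the resampled 3 mm voxel that is 2/3 = 0.67. Against the acquired in-plane voxel, 240/64 = 3.75 mm, it is 2/3.75 = 0.53. This is the largest movement allowed, not the typical one, so it shows only that retained scans are not motion-free.

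**Size of a spurious difference.** Let r be the within-arm correlation between a processed map value and a participant's mean motion, after all preprocessing. Let d be the arm difference in mean motion in SD units. Both are assumptions. The shift between arms in outcome SD units is

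shift = r × d.

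For a two-sample t-test with n = 25 per arm, there are 2n − 2 = 48 degrees of freedom and the noncentrality is r × d × √(n/2) = r × d × √12.5. The rejection rate with no true drug effect comes from the noncentral t distribution. The two-sided critical value is 3.505 at 0.001 and 2.011 at 0.05.

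| r | d | shift (SD) | noncentrality | rate at voxel 0.1% | rate at 5%, one region |
|---|---|---|---|---|---|
| 0 | any | 0 | 0 | 0.10% | 5.0% |
| 0.1 | 0.2 | 0.02 | 0.071 | 0.10% | 5.1% |
| 0.1 | 0.5 | 0.05 | 0.177 | 0.12% | 5.3% |
| 0.3 | 0.2 | 0.06 | 0.212 | 0.12% | 5.5% |
| 0.3 | 0.5 | 0.15 | 0.530 | 0.27% | 8.1% |
| 0.5 | 0.5 | 0.25 | 0.884 | 0.71% | 13.9% |

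The voxel column corresponds to the plan's stated voxel threshold. The 5% column is for scale only, because the plan contains no single-region test at 5%. I did not compute a cluster-level error rate: it depends on the spatial pattern of residual motion effects, which the documents do not give.

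**Effect on precision.** Adjusting for motion removes r² of the between-participant variance: 1% at r = 0.1, 9% at r = 0.3 and 25% at r = 0.5.

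**Cost in degrees of freedom.** With 50 scans, arm plus age and sex leaves 46 and adding mean displacement leaves 45. The critical value at 0.001 moves from 3.505 (48 df) to 3.520 (45 df).

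**The case against.** The strongest reply is that the plan already takes motion seriously: instructions at acquisition, realignment, an exclusion rule, and regression of 24 motion parameters with three further nuisance signals. A reader might infer that every arm difference in motion enters the results as a drug effect. The documents do not support that, because only motion effects surviving those steps can bias the test, and with r = 0 there is no bias whatever the arms do. This part of the objection stands and limits the point.

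Second, a reader might infer that the imaging outcomes are certainly left unadjusted. That is also too strong. The opening statement in 20a about adjusting for age, gender, BMI and HAMD is not restricted to non-imaging outcomes, although the imaging sentence then names a test that takes no covariates. The text is ambiguous on those variables. It is not ambiguous on motion, which neither list contains.

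Third, a nuisance covariate could be regarded as detail that an article leaves to the full protocol or analysis plan. Here, however, the article names the test, the software and the thresholds, and describes preprocessing down to the smoothing kernel. The plain t-test is a stated choice, not a gap.

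Fourth, motion on treatment is a post-randomisation variable. If treatment alters it, conditioning on it changes what is estimated and may introduce bias of its own. This stands. It is a good reason not to make the motion-adjusted model the only lead analysis, but not a reason to have no such analysis.

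**Conclusion.** The point holds in a limited form. Motion control stops at the level of the individual scan, the stated group test is a two-sample t-test without a motion term, and no stated analysis would tell a residual motion artefact from a brain effect of liraglutide.

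The size cannot be derived from the documents. For arm differences in motion of 0.2 to 0.5 SD and 25 scans per arm, it runs from negligible (0.10% to 0.12% at the 0.1% voxel threshold, if the residual correlation is 0.1) to about 0.7% at that threshold (if the correlation and the arm difference are both 0.5). The documents neither state nor imply where in that range the trial would fall, or that the arms will differ in motion at all. The change is worth making because it is nearly free and concerns a primary outcome, not because a large bias has been shown.

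**What to change.** In section 20a, replace the plain two-sample t-test with a voxel-wise linear model for arm, adjusted for the baseline covariates already named there (at least age and sex), and keep the stated Gaussian Random Field thresholds. Pre-specify the same model with each participant's mean framewise displacement added, and report the two side by side. State in advance that an imaging effect will be called robust only if it persists with motion adjustment. Tabulate mean displacement and the number of scans excluded for motion by arm.

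The cost is two or three sentences and a few degrees of freedom. No new data are needed, since displacement comes from the realignment parameters already estimated and age and sex are already collected. The sample size of 60 does not change. The main downside is that, if the drug itself alters motion, the motion-adjusted estimate may remove a drug-mediated part; this is why both models are shown. Settling it before unblinding avoids a post hoc choice between them.
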